HYPOTHESIS 

The hypothesis to be tested is that a randomized, controlled treatment trial of antibiotic treatment for adult asthma
can be carried out successfully in a geographically dispersed
practice-based research network.

The secondary hypothesis is that trends favoring antibiotic treatment will emerge
during followup, allowing estimation of sample size(s) for an adequately powered study protocol to be submitted to the National Institutes of Health (NIH) as an RO-1 grant.

        ABSTRACT

Asthma is a chronic inflammatory bronchial condition of unknown
etiology.  Decades ago many clinicians believed that infection played a
major role in asthma etiology, but current expert opinion favors the view
that asthma is a noninfectious condition whose root cause is
inflammation.  Therefore chronic antiinflammatory therapy, mainly inhaled
corticosteroids, is currently advocated as primary anti-asthma treatment. 
It is important to recognize, however, that antiinflammatory therapy is
palliative, not curative.

A growing body of evidence implicates chronic bronchial infection with
Chlamydia pneumoniae in the pathogenesis of asthma in both adults and
children.  Organism identification studies (culture and PCR) suggest that
up to one-half of children with asthma may be chronically infected by C.
pneumoniae, and seroepidemiologic studies in adults are consistent with
chronic C. pneumoniae infection in the majority of adult-onset asthmatics.
 Furthermore, case reports and uncontrolled trials have provided
provocative but inconclusive evidence that treatment of C. pneumoniae
infection in both children and adults with asthma can favorably affect the
natural history of this disorder.

We propose a randomized, placebo-controlled, triple-blinded study of
antichlamydial antimicrobial therapy in adult asthma.  Results will
help to determine whether antimicrobial therapy is effective in treating
some adult asthma syndromes.  Positive results would have significant
public health implications.  Methodologies developed for use in this trial
may expedite future studies in practice-based research networks.

BACKGROUND AND METHODS 

1.  BACKGROUND AND PURPOSE  Asthma is a chronic inflammatory lung
condition of unknown etiology.  The cost for asthma care in the US has
been conservatively estimated at over $6 billion (1990 data) with 55% of
costs attributable to asthma in patients 18 years or older.1  Currently
recommended antiinflammatory therapies are palliative, not curative2 and
asthma morbidity and mortality appears to be increasing in recent
decades.3

An emerging body of evidence suggests that chronic Chlamydia
pneumoniae respiratory tract infection may be responsible for the
bronchial inflammation underlying some asthma syndromes,4 including
adult-onset asthma.5  Preliminary reports of complete asthma remission
following prolonged treatment with macrolides and tetracyclines
(effective against chlamydia) raise the possibility of "cure" for some
patients with the infectious asthma syndrome.6  An analogy with
Helicobacter pylori infection as a cause of peptic ulcer disease is
suggested.  Our primary goal is to test the feasibility
of performing a randomized antibiotic treatment trial in a geographically dispersed
practice-based research network (PBRN) where the majority of asthma
is encountered and managed.1  Our secondary goal is to determine in this controlled trial whether
addition of antibiotic treatment to usual care for adult-onset asthma is
superior to placebo.

PRIMARY OBJECTIVE  To test the feasibility of implementing the trial
in a practice-based research network.  The specific feasibility questions
to be addressed are: (1) Can the PBRN practices successfully recruit
and enroll eligible participants? (2) Can the central coordinating site
develop and maintain practice interest? (3) Can patient-reported data
collection be facilitated by use of an interactive voice-response (IVR)
telephone system, thus relieving the PBRN practices of responsibility for
most data collection and management?

SECONDARY OBJECTIVE  To perform a randomized, triple-blinded
(physician, patient and data analyst) controlled trial of antibiotic treatment
for adult asthma.

PREVIOUS AND RELATED WORK  The PI for this project has published
the majority of articles associating asthma with chronic chlamydial
infection.4

His first major publication to describe this association (partially funded by
the AAFP) was successfully performed in non-academic primary care
clinics from a single geographic area.5  The PI has also successfully
performed a study describing adult-onset asthma prevalence with the
active cooperation of 60 geographically dispersed PBRN practices.7  A
study currently recruiting adult asthma patients for a randomized trial of
macrolide treatment in New Zealand, Australia and Argentina has
confirmed that 60% of 459 adults with asthma (mixture of adult- and
childhood-onset) have antibody levels indicative of possible chronic
infection with Chlamydia pneumoniae ([name]: personal
communication).  Thus it is important to proceed with randomized trials in
North America, since results of several trials might have a significant
effect on asthma management worldwide.

METHODS  
1. Patient selection criteria: Adults (ages 18 and older) with stable
chronic (>3 months duration) persistent asthma as defined by the
updated Expert Panel Report (EPR2)2 are eligible for enrollment. 
Patients will not be enrolled during an asthma exacerbation.  Stability of
asthma must be demonstrated during a two-week (pre-randomization)
run-in period.

2. Study setting: Primary care (mostly family practice) clinicians in
Wisconsin and elsewhere in North America were recruited from (1) the
Wisconsin Research Network (WReN), (2) participants in a previous
asthma prevalence study7 and (3) participants from an interest group at
the 1997 ASPN Annual Convocation of Practices.  See Appendix 1 for a
list of study participants.  Clinics in an urban area will be included to
increase representation of indigent non-white asthma patients.

3. Sample size: We plan to accrue 100 evaluable patients in this pilot
study.  We expect to enroll at least 6 eligible patients per site from 20
sites (20% dropout rate).  We estimate that the incidence of adult-onset
asthma is 1/1000/year8 and that the average primary care practitioner
cares for 1000 adults (a conservative estimate).  Therefore, a five
person primary care group practice will have in their patient population
approximately 50 potentially eligible adult-onset asthma patients whose
disease duration is ten years or less in addition to a greater number of adults with asthma that began in childhood.

The sample size for this pilot was determined by feasibility issues, e.g.,
by an estimate of the number of patients we can afford to enroll with the
limited funds available.  Adult-onset asthma patients are more likely to exhibit serologic
evidence of chronic C. pneumoniae infection than patients with a history
of childhood-onset asthma.4  A detailed but speculative power analysis
(available by request) suggests that a total sample size in the range of
several hundred patients is desirable.  This estimate depends on several
variables including the C. pneumoniae seroprevalence in the target
population, the duration of symptomatic disease prior to treatment and the
amount of fixed obstruction accompanying the asthma.6

4. Study design: Randomized, placebo-controlled trial of azithromycin
(600 mg orally, daily for 3 days, then once per week for an additional 5 weeks (total dose 4800 mg) v. matching placebo
added to usual care for asthma.  The antibiotic regimen was chosen
based on the results of a previous open-label study demonstrating
persistent improvement in asthma after azithromycin therapy.6  Usual care is
defined as the care usually provided to asthma patients at the study site. 
Efficacy will be determined at 3 months post-treatment completion.

5. Outcome measures: Patient-reported measures include (1) a generic
and a disease-specific quality-of-life (QOL) questionnaire and (2) asthma
diary data, including symptoms, function, bronchodilator use and diurnal
peak expiratory flow rate (PEFR).  Clinician-derived measures include (1)
clinician assessments and (2) pre-bronchodilator FEV1.  The generic
QOL questionnaire will be the SF-36 which has been validated for
asthma.9  The disease-specific instrument of Juniper et. al. has been
extensively used in prior asthma research and will be employed in this
study.10  The patient diary incorporates standard measures of asthma
symptoms, bronchodilator use and PEFR used in previous studies, as
well as validated daily function measures that may supplement SF-36
information11 (Appendix 2).  The primary outcome measure will be
difference (azithromycin v. placebo) in pre-bronchodilator FEV1 at the
3-month post-treatment visit.  The secondary measures will be
differences in bronchodilator use, clinical status (exacerbations requiring
steroid administration, emergency facility use and/or hospitalization) and
QOL.  Outcomes will be post-stratified on evidence/no evidence of C.
pneumoniae infection.  Evidence of infection is defined as a positive PCR in peripheral blood mononuclear cells
and/or an IgG titer of 1:64 or greater and/or an IgA titer of 1:16 or
greater.

6. Visit schedule: Five visits over 5 months are planned: visit 1 (entry
visit, week -2) for initial eligibility assessment and informed consent; visit
2 (randomization, week 0) for final eligibility assessment, pre-treatment
clinical results, pre-bronchodilator FEV1 and chlamydia studies, and
dispensing of study medication; visit 3 (mid-therapy, week 3) to assess
initial compliance and side effects; visit 4 (end-therapy, week 6) to
assess final compliance and side effects; and visit 5 
(follow-up, week 18, 3 months after finishing study treatment) to record
post-treatment clinical results, pre-bronchodilator FEV1 and chlamydia
studies.  Clinical results will include (1) history of exacerbations requiring
steroid administration, emergency facility use and/or hospitalization, (2) changes in bronchodilator and other asthma medication use and (3)
global assessment of asthma severity score validated in a previous
study.6  Chlamydia studies will include C. pneumoniae-specific (1)
polymerase chain reaction (PCR) testing of peripheral blood mononuclear cells and
(2) serology (IgG and IgA).

7.  Interactive voice-response system: Interactive voice response
telephone systems have become a routine part of daily life for most
Americans who make airline reservations or call banks and other
businesses including medical offices.  Sophisticated IVR systems to
diagnose and manage psychiatric conditions, including depression and
obsessive-compulsive disorder, have been developed and tested at the
Dean Foundation for Health Research and Education, Madison,
Wisconsin.12  The generic software drivers used in the existing
applications can be readily adapted for use in data collection for asthma
studies (Appendix 3).  All patient-reported data (QOL questionnaires and
diary information) will be recorded directly by patients into the IVR
system databank using a toll-free 800 number.  The IVR system has
several advantages over traditional data collection methods: (1) data is
entered directly into digital format, avoiding data entry errors, (2)
practices are not burdened by data collection tasks, (3) patient
compliance can be monitored systematically, (4) patients can dial in from
anywhere in the world, and (5) previous experience indicates that
patients offer as much or more information to computerized IVR systems
as they do during face to face interviews with clinicians.12

8. Statistical testing:  Between group comparisons (active drug v.
placebo) will be performed using an unpaired t-test for normally
distributed continuous data and the nonparametric Mann-Whitney U test
for non-normally distributed ranked data.  Within group differences
(followup compared to baseline) will be performed using the paired t-test
for normally distributed continuous data and the Wilcoxon signed rank
test for non-normally distributed ranked data.  Multivariate modelling of
normally distributed continuous dependent variables (to control for
discrete and/or continuous covariates as needed) will be performed
using ANOVA and/or ANOCOVA.  Logistic regression will be used to
control for confounding when the dependent variable of interest is a
noncontinuous bivariate.  Other tests, including Fishers exact test for 2 x
2 tables and the chi-square test for n x r tables, will be used when
appropriate.

9. Study flow diagram

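### The default test for the primary outcome measure, FEV1 at week 18, is an unadjusted t-test; adjustment for the FEV1 measured at randomization is permitted but not fixed

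*Protocol*

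**What the plan says.** Protocol, Methods, section 5 (Outcome measures) defines the primary outcome measure as the "difference (azithromycin v. placebo) in pre-bronchodilator FEV1 at the" 3-month post-treatment visit. This is a follow-up value, not a change from baseline.

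Section 6 (Visit schedule) places the same measurement at both ends of the trial. Visit 2, at randomization, covers pre-treatment "clinical results, pre-bronchodilator FEV1 and chlamydia studies, and" dispensing of medication. Visit 5 is described as "follow-up, week 18, 3 months after finishing study treatment) to record" post-treatment results, FEV1 among them.

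Section 8 (Statistical testing) lists methods by type of data:

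- Between groups: "placebo) will be performed using an unpaired t-test for normally" distributed continuous data, and Mann-Whitney for non-normal ranked data.
- Within groups: "followup compared to baseline) will be performed using the paired t-test" or the signed rank test. This is the only place in the section where baseline is named.
- Modelling of normally distributed continuous outcomes, to control for "discrete and/or continuous covariates as needed) will be performed" "using ANOVA and/or ANOCOVA". No covariate is named, and nothing says when adjustment is needed.

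Section 3 (Sample size) states "We plan to accrue 100 evaluable patients in this pilot" study, a number set by funds and not by a power calculation. The Hypothesis and Objectives sections make feasibility primary and efficacy secondary. They expect trends in the data to support sample-size estimation for a later, adequately powered trial.

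**The concern.** FEV1 differs between adults with asthma for reasons unrelated to the study drug, including the fixed obstruction that section 3 itself mentions. In a stable population, a patient's FEV1 at randomization should predict much of that patient's FEV1 at week 18. A comparison of week-18 values alone leaves all of that predictable variation in the error term. Adjusting for visit-2 FEV1 removes it, using data the trial already collects.

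Two things are at stake. The first is the precision of the efficacy estimate in a trial that the protocol itself regards as smaller than desirable. The second is what the pilot hands on: an effect estimate and a standard deviation for sizing the next trial. An unadjusted standard deviation would lead to a larger trial than an adjusted analysis needs.

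Leaving three routes open (t-test, rank test, adjusted model) also means that no single result is identified in advance as the primary one.

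**Working it through.** **The plan's own figure.** Section 3 plans 100 evaluable patients from at least 6 at each of 20 sites with 20% dropout. 6 × 20 = 120, and 120 × 0.80 = 96, not 100; 100 / 0.80 would need 125 enrolled. Because 6 per site is a minimum, 120 is a floor. The gap is immaterial here, so I use the stated 100, or 50 per arm. The 1:1 ratio is an assumption; the document gives none. There is no stated power, effect size or SD to reproduce.

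**Assumed inputs, not in the document.** Correlation ρ between visit-2 and week-18 FEV1 of 0.6 to 0.9; two-sided 5% level; 80% power; normal approximation. Results are in units of the between-patient SD of week-18 FEV1, so they do not depend on whether FEV1 is in litres or percent predicted, except through ρ.

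**Formulas.**

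- SE of the unadjusted difference = √(2/50) = 0.20 SD. The 95% half-width is 1.96 × 0.20 = 0.39 SD. The detectable difference is (1.96 + 0.84) × 0.20 = 0.56 SD.
- Adjusting for baseline multiplies the SE by √(1 − ρ²). The equivalent number of patients is multiplied by 1/(1 − ρ²).

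| Analysis | SE multiplier | Equivalent patients | 95% half-width (SD) | Detectable difference (SD) | Power for 0.4 SD |
|---|---|---|---|---|---|
| Unadjusted t-test | 1.00 | 1.0 × | 0.39 | 0.56 | 52% |
| Adjusted, ρ = 0.6 | 0.80 | 1.6 × | 0.31 | 0.45 | 71% |
| Adjusted, ρ = 0.7 | 0.71 | 2.0 × | 0.28 | 0.40 | 80% |
| Adjusted, ρ = 0.8 | 0.60 | 2.8 × | 0.24 | 0.34 | 92% |
| Adjusted, ρ = 0.9 | 0.44 | 5.3 × | 0.17 | 0.24 | >99% |

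With 48 per arm (from the 96 above), the unadjusted detectable difference is 0.57 SD instead of 0.56. The multipliers do not change.

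**Cost of estimating the slope.** For a normally distributed covariate, the expected variance is inflated by 1 + 1/(98 − 2) = 1.01. Adjustment therefore loses only if (1 − ρ²) × 97/96 exceeds 1, that is, if ρ is below √(1/97) = 0.10.

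**Effect on the next trial.** To detect 0.3 SD with 80% power, the total is 4 × (1.96 + 0.84)² / 0.3², which is 350 patients after rounding up per arm. Multiplying by 1 − ρ² gives 178 at ρ = 0.7 and 126 at ρ = 0.8.

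**The case against.** The best defence is that section 8 does not exclude the better analysis. It provides for analysis of covariance with continuous covariates, and visit-2 FEV1 would qualify. No test is tied to FEV1 by name: that the primary comparison is a t-test on the week-18 value comes from reading sections 5 and 8 together. The choice of covariates is often left to an analysis plan, and one may exist. Efficacy is a secondary objective of a feasibility pilot, and no power claim rests on the t-test.

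Most of this stands, and it limits the point. A reader might infer three stronger claims that the document does not support:

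- That the plan ignores baseline FEV1. It does not, since adjustment is permitted.
- That the choice of test would be made after seeing the data. The protocol does not say when adjustment would be decided, and the Secondary objective blinds the data analyst. Blinding limits selection towards a favoured arm, though it does not designate one analysis as primary.
- That chance baseline imbalance is a further harm, or biases the unadjusted result. Under randomization the t-test is unbiased, and its SE already contains that imbalance. At ρ = 0.8 the imbalance carried through has an SD of 0.8 × 0.20 = 0.16, and the adjusted SE is 0.6 × 0.20 = 0.12. Since 0.16² + 0.12² = 0.20², the imbalance is the precision loss, counted once.

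What the defence does not answer is that the protocol is not silent. It states a default test, and that default is the less precise of the two methods it offers for this outcome.

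**Conclusion.** The point holds as one of efficiency and pre-specification. Read together, sections 5 and 8 make an unadjusted comparison of week-18 values the default for the primary outcome measure. They permit adjustment for visit-2 FEV1 without naming that covariate or saying which analysis is primary.

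The unadjusted result would be valid but less precise. Its size rests on ρ, which the document does not give: the adjusted SE is 0.80 to 0.44 of the unadjusted one for ρ from 0.6 to 0.9. A low ρ seems unlikely, because patients must have stable chronic asthma confirmed over a two-week run-in and the readings are only 18 weeks apart, but that is a judgement. The absolute figures also assume 50 per arm.

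The change should be made, but the trial's primary, feasibility objective is unaffected. The benefit goes to the secondary objective and to the planning of the next trial.

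**What to change.** In section 8, or in the analysis plan if there is one, name a single primary efficacy analysis: analysis of covariance of week-18 pre-bronchodilator FEV1 on treatment group, with visit-2 pre-bronchodilator FEV1 as covariate, reported as an adjusted mean difference with a 95% confidence interval. Remove the as-needed condition for this outcome. Keep the unpaired t-test and the Mann-Whitney test as sensitivity analyses.

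Report the residual SD and the observed baseline to week-18 correlation as well, since these are what the next trial's sample size needs.

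The cost is a sentence or two of text and one degree of freedom (97 residual instead of 98 with 100 patients). No new data or visits are required.

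### Section 8 plans within-arm significance tests of follow-up against baseline and does not keep them out of the efficacy claim

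*Protocol*

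**What the plan says.** Section 8 of the protocol (Statistical testing) lists its analyses in this order:

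- Between-group comparisons, active drug against "placebo) will be performed using an unpaired t-test for normally" distributed data, with the Mann-Whitney U test as the alternative.
- Within-group comparisons, "followup compared to baseline) will be performed using the paired t-test", with the Wilcoxon signed rank test as the alternative.
- Multivariable modelling "using ANOVA and/or ANOCOVA. Logistic regression will be used to" handle binary outcomes. Covariates are to be added as needed; the baseline value is not named as one.

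Section 5 (Outcome measures) defines the primary outcome as the "difference (azithromycin v. placebo) in pre-bronchodilator FEV1 at the" visit three months after treatment. The secondary measures are likewise "differences in bronchodilator use, clinical status (exacerbations requiring" steroids, emergency care or hospital admission) and quality of life.

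The Hypothesis section adds: "The secondary hypothesis is that trends favoring antibiotic treatment will emerge" during follow-up, so that the sample size of a later, adequately powered trial can be estimated.

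The protocol does not say what the within-group tests are for. It neither calls them descriptive nor excludes them from efficacy statements.

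**The concern.** A paired test inside one arm makes no use of the placebo group. FEV1 is measured at week 0 and again at week 18, with study drug added to whatever usual care the site provides. Season, closer attention, changes in other asthma medication and regression to the mean can move both arms between those visits. A within-arm p-value cannot separate them from a drug effect.

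The practical risk is the familiar one of comparing two p-values: azithromycin improved significantly, placebo did not, therefore the drug works. Three features of this protocol make that reading tempting.

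- The word trend in the secondary hypothesis is not defined.
- The sample size was set by funds, and section 3 says several hundred patients would be desirable, so the between-arm comparison may well be inconclusive.
- The trends are meant to size the next trial, so a change from baseline mistaken for a treatment effect would carry over into that calculation.

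**Working it through.** The protocol gives no significance level, power, effect size or standard deviation, so there is no figure of its own to reproduce. The calculation below only sizes the misreading described above, should it occur.

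**Inputs**

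- Number per arm. Section 3 says "We plan to accrue 100 evaluable patients in this pilot" study. The allocation ratio is not stated; equal allocation is assumed, giving 100 / 2 = 50 per arm. The recruitment figures in the same section give slightly fewer: 20 sites × 6 patients = 120, and 120 × (1 − 0.20) = 96, or 48 per arm. Both are used.
- Two-sided 5% tests: assumed.
- No drug effect: both arms share the same mean change d, expressed in SDs of the change score. The protocol gives no value for d, so it is varied from 0 to 0.5.

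**Formulas**

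- For each arm the paired t statistic follows a noncentral t distribution with n − 1 degrees of freedom and noncentrality d√n. The critical value is 2.010 for n = 50 and 2.012 for n = 48.
- Let u be the probability of a significant improvement, and p the probability of a significant change in either direction.
- The arms are independent, so P(azithromycin significantly improved, placebo not significant) = u(1 − p).
- P(exactly one arm significant) = 2p(1 − p).

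**Example, n = 50, d = 0.2.** Noncentrality = 0.2 × √50 = 1.414; u = 0.2832; p = 0.2836. Then u(1 − p) = 0.2832 × 0.7164 = 0.203, and 2p(1 − p) = 2 × 0.2836 × 0.7164 = 0.406.

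**Results with an inactive drug**

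| Common change d (SD) | Azithromycin improved, placebo not: n = 50 | Same: n = 48 | Exactly one arm significant: n = 50 |
|---|---|---|---|
| 0 | 2.4% | 2.4% | 9.5% |
| 0.1 | 9.2% | 9.0% | 19.1% |
| 0.2 | 20.3% | 19.9% | 40.6% |
| 0.28 | 25.0% | 24.9% | 50.0% |
| 0.4 | 16.5% | 17.5% | 33.0% |
| 0.5 | 6.2% | 7.0% | 12.4% |

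The maxima, 25% and 50%, occur where each arm has an even chance of reaching significance (p = 0.5), since u is then practically equal to p. Here that is at about d = 0.28.

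**Comparison with the between-arm test.** In 40,000 simulated trials at each of d = 0, 0.2, 0.277 and 0.4 (n = 50), the unpaired t-test on the change scores was significant in 4.9% to 5.1%, and significant in favour of azithromycin in about 2.5%. The common change cancels in the difference between arms, so the size of d does not matter.

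**The case against.** A reader might infer that the plan judges efficacy from change within each arm, and so may find an effect where none exists. The protocol does not support that. Its primary outcome is a difference between azithromycin and placebo, its stated secondary goal (Background and purpose) is superiority over placebo, and section 8 puts the between-group tests first. Nowhere does it say that efficacy will be concluded from within-group p-values or from setting them side by side. Running them in addition does not change the error rate of the primary comparison. In a placebo-controlled trial, a trend favouring antibiotic is most naturally a comparative statement. All of this stands.

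A reader might also take 20% to 25% as the expected error rate. That holds only for a common change of about 0.2 to 0.3 SD, which is where the curve peaks; no value is given in the protocol. Section 1 (Patient selection criteria) requires stable asthma shown over a two-week run-in and excludes enrolment during an exacerbation, which limits regression to the mean. A smaller shift, and a smaller error, is plausible.

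Finally, this is a pilot whose primary objective is feasibility, and a statistical analysis plan not shown here may settle the role of secondary tests. That lowers the weight of the point. It does not remove it: the protocol itself already fixes these significance tests, leaves their use open, and the tests cannot answer whether azithromycin beats placebo.

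**Conclusion.** The point holds in a limited form. Section 8 plans within-arm significance tests that disregard the control group, and the protocol does not restrict what may be concluded from them. The primary comparison is correctly specified and unaffected.

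The harm is conditional on use. If significance on azithromycin but not on placebo were taken as an effect, the false-positive chance in favour of azithromycin would lie between about 2% and 25% for common changes of 0 to 0.5 SD, against about 2.5% for the between-arm test. This rests on equal allocation, 48 to 50 evaluable patients per arm, two-sided 5% tests, normally distributed changes and the same mean change in both arms, none of which the protocol states. The change is worth making because it costs almost nothing and puts a more useful estimate in place of an uninformative test.

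**What to change.** In section 8, replace the sentence on within-group testing with a statement that changes from baseline will be summarised in each arm (for example mean change and SD) without p-values and as description only.

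Add one sentence: every efficacy statement, including any trend used to estimate the size of the next trial, rests on the between-arm difference with its 95% confidence interval. For the primary outcome, obtain that difference by analysis of covariance (the protocol's ANOCOVA) of FEV1 at the three-month post-treatment visit, with week 0 FEV1 as covariate. Treat other continuous outcomes in the same way where a baseline value exists.

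The cost is two or three sentences and fewer tests to run. Naming the baseline covariate is a small change to the analysis in its own right, but the method is already listed in section 8 and week 0 FEV1 is already collected at visit 2, so no new data, visits or patients are needed.
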